## Abstract

**Background:**

Blind/low vision (BLV) severely limits information about our three-dimensional world, leading to poor spatial cognition and impaired navigation. BLV engenders mobility losses, debility, illness, and premature mortality. These mobility losses have been associated with unemployment and severe compromises in quality of life. VI not only eviscerates mobility and safety but also, creates barriers to inclusive higher education. Although true in almost every high-income country, these startling facts are even more severe in low- and middle-income countries, such as Thailand. We aim to use VIS^4^ION (Visually Impaired Smart Service System for Spatial Intelligence and Onboard Navigation), an advanced wearable technology, to enable real-time access to microservices, providing a potential solution to close this gap and deliver consistent and reliable access to critical spatial information needed for mobility and orientation during navigation.

**Methods:**

We are leveraging 3D reconstruction and semantic segmentation techniques to create a digital twin of the campus that houses Mahidol University’s disability college. We will do cross-over randomization, and two groups of randomized VI students will deploy this augmented platform in two phases: a passive phase, during which the wearable will only record location, and an active phase, in which end users receive orientation cueing during location recording. A group will perform the active phase first, then the passive, and the other group will experiment reciprocally. We will assess for acceptability, appropriateness, and feasibility, focusing on experiences with VIS^4^ION. In addition, we will test another cohort of students for navigational, health, and well-being improvements, comparing weeks 1 to 4. We will also conduct a process evaluation according to the Saunders Framework. Finally, we will extend our computer vision and digital twinning technique to a 12-block spatial grid in Bangkok, providing aid in a more complex environment.

**Discussion:**

Although electronic navigation aids seem like an attractive solution, there are several barriers to their use; chief among them is their dependence on either environmental (sensor-based) infrastructure or WiFi/cell “connectivity” infrastructure or both. These barriers limit their widespread adoption, particularly in low-and-middle-income countries. Here we propose a navigation solution that operates independently of both environmental and Wi-Fi/cell infrastructure. We predict the proposed platform supports spatial cognition in BLV populations, augmenting personal freedom and agency, and promoting health and well-being.

**Trial registration:**

ClinicalTrials.gov under the identifier: NCT03174314, Registered 2017.06.02.

## Introduction

### Background and rationale {6a}

#### An international perspective on visual disability

Globally, there are 39 million blind and 246 million visually impaired people [1]. The economic impact of visual impairment was estimated to approach $3 trillion [2]. Assistive technologies enable people to be more productive, more independent, and achieve a higher quality of life. Despite the benefits derived from assistive technologies (AT), some parts of the world have minimal or no access to AT. In many low-income and middle-income countries (LMIC), only 5–15% of people who require AT have access to them. Rapid demographic changes will exacerbate this situation as populations over 60 years of age in LMIC are expected to be higher than in high-income countries in the coming years. Given both these trends, ATs are likely to be in high demand and help in our response to aging and disability.

According to Thailand’s National Statistical Office, visual disability is the third most common type of disability. Around 192,640 persons (or about 9%) have a visual disability who qualify for special rights, including 57,520 in the 15–59 age bracket, 2027 in the 6–14 range, and the remainder over 60. While therapeutic advances are in the “pipeline” for a handful of conditions, there are a multitude of causes that engender severe visual disability [3, 4], and the prevalence of many of these conditions is on the rise [5]. In addition to impaired mobility [6–8], vision impairments lead to unemployment [9], quality of life loss [10–12], and functional dependency [13], all of which reduce psychosocial well-being. More than 60% of visually impaired adults in Thailand face problems related to independent mobility, domestic activity, and performing activities of daily living [14]. Thai students with VI face barriers in day-to-day activities related to blind unfriendly physical structures, particularly those on educational campuses [15]. VI has also been associated with depression, decreased physical activity, impaired balance, and falls in Thailand [16, 17].

#### Increasing mobility: a persistent challenge

The concept of mobility is an essential aspect for all citizens. Given the development of cities, the complexity of successfully navigating between locations increases each day. Although there exists a potpourri of possible solutions to help promote mobility for the general citizen, there are particular design considerations for people with blindness and low vision.

Overall, mobility and wayfinding are difficult and often riddled with danger for people with BLV, especially in urban areas. The last century has seen the development of many accessibility devices and applications to assist BLV individuals, but few have been widely adopted; the white cane and guide dog are still the most commonly used mobility tools [18]. The use of a device is dependent on its characteristics, the application domain, and the user. In general, simple devices employed for use during seated tasks have the highest continued usage (60–80%) [19, 20], while those for augmentation of daily living activities and mobility have had much lower long-term usage rates (less than 20%) [21]. One possible explanation for the low acceptance of past efforts could be due to not sufficiently addressing users’ needs. As a result, most blind and low-vision students spend time after school alone without interacting with others [22]. In higher educational settings, many blind-unfriendly physical environments on campus have been documented but not addressed due to the challenging and expensive nature of the barriers, as a result, students are discouraged from active social participation as such environments seriously hamper their ability to join in lecture-based interactions and social gatherings [23]. These are disheartening facts, since many BLV live in cities with multiple universities and many social opportunities, and have the potential to engage with rehabilitation services, employment opportunities, and public transportation [24].

Since the Thailand Rehabilitation Act of 1991, medical rehabilitation services for people with disabilities are increasingly available around the country. The Rehabilitation Act was subsequently renamed the Persons with Disability Empowerment Act in 2007 and orientation and mobility services are included within a universal health benefits package, along with white canes. However, while there has been a push in Thailand for the digitalization of society, there has not been any research and development on digital assistive technologies to improve mobility.

#### Wearable solutions: a paradigm shift

In our current era of self-driving vehicles, there is a clear need to move beyond the traditional approaches, such as the white cane, used in conjunction with a mélange of limited-use gadgets and apps. We propose a paradigm shift focused on comprehensive tools to make safe mobility a reality for the BLV. The long-term goal of our research team is to improve the quality of life of individuals who are adapting to low vision and blindness by providing connected, human-in-the-loop wearable solutions that foster true functional independence.

#### Spatial intelligence: user-centered design to improve outcomes

VIS^4^ION, a mobile computing platform capable of real-time scene understanding with human-in-the-loop navigation assistance, has four components: (1) a wearable**/**instrumented backpack with several distinct distances and ranging/image sensors to extract pertinent information about obstacles and the environment; (2) an embedded system (Edge AI-computer) with both computing and mobile (4G, 5G, and Wi-Fi) communication capability (*inside backpack*); (3) a haptic interface (waist strap) that communicates the spatial information computed from the sensory data to the end-user in real-time via an intuitive, torso-based, ergonomic, and personalized vibrotactile scheme; and (4) a headset that contains both binaural bone conduction speakers and a noise-canceling microphone for oral communication [25, 26]. The belt and headset are used to alert the end user of environmental features. A stereo camera is our main image sensor and acts as a sensing foundation. Advanced computer vision algorithms are deployed on the Nvidia Jetson Xavier processor board for continuous analysis of a dynamically changing environment [25, 26].

The platform delivers a series of microservices to the end user. One basic feature is hazard-mapping. The scene, as viewed by the stereo camera, is decomposed into capture fields that correspond to the density of the tactors on the haptic interface in a spatiotopically preserved, intuitive, body-centered (egocentric) fashion (Fig. 1). Shorter hazards vibrate fewer (lower) actuator columns on the belt and obstacles that are closer to the user induce a higher frequency of vibration, giving a sense of tactile looming or “approach.”

**Fig. 1 Fig1:**
[figure not shown]
(Top) a simulated view of a scene decomposed into capture fields that spatiotopically correspond to actuators in the haptic interface; (bottom) color-coded depiction demonstrating the scene decomposed into a segmented grid for belt-based vibratory warnings of various threat levels based on proximity and spatial position (note: 12 tactors correspond to 12 capture fields)

With its user-friendly form factor, the platform is easily adoptable by BLV individuals. Yet, there is a pressing need to expand its function by refining its mapping/localization microservices and steering its development toward a defined social problem to fill the following gaps: (1) limited ability to interpret real-world scenes through computer vision algorithms and excessive computational burden (mapping); (2) lack of a scientifically-principled, experimentally-based understanding of users’ needs and behavioral patterns in complex settings, such as Thailand; (3) poor understanding of the implementation methods required to deploy and sustain such mapping and localization methods at scale effectively; and (4) lack of hypotheses-driven studies with ecological validity.

### Explanation for choice of comparators {6b}

This study aims to test the hypothesis that VIS^4^ION is a wearable assistive technology that assists spatial cognition in VI populations, enhancing personal freedom and independence, health, and well-being. VIS^4^ION is able to take advantage of contemporary, state-of-the-art technologies and approaches. The backpack embodiment was a careful decision made with end users to enhance acceptance; user-centric design approaches will be used for the entirety of the project.

There is a clear lack of comparison of the effect of wearable assistive technology on health and quality of life, including independent and social engagement in active and passive mode; trials evaluating the effectiveness of assistive technology rarely included mobility metrics, subjective and objective assessments of the quality of life, acceptability and appropriateness as comparators. Therefore, we will have comprehensive metrics to evaluate the outcomes in the first week and fourth week of extended use of wearables in passive and active phases. In “the passive phase,” the wearable will be maintained in a monitoring mode and simply acquire data, providing no assistance/feedback on location and orientation. During the active phase, the wearable will have an activated assistive mode, i.e., the wearable will acquire data and simultaneously provide assistance/audio feedback.

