Each FGD session will last roughly 60 min and include participants’ perceptions and experiences while navigating the VIS^4^ION system. The FGDs will be guided by pre-determined questions related to general perceptions of the VIS^4^ION system, as well as thoughts on the facilitators and barriers of the intervention. The FGD sessions will be audio-recorded verbatim and later transcribed and translated into English by the research team. During the sessions, the research team member will also take field notes.

#### Aim 4

A cohort of 20 (new) participants will be recruited to assess extended-use benefits over one month. We will create two groups for the randomized crossover design. Each participant will be randomized to either sequence A (10 participants) or sequence B (10 participants). During the first 15 days, group A will go through an active phase and then a passive phase for the next 15 days. Reciprocally, group B will go through a passive phase for the first 15 days and then an active phase for the second half of the month. During the passive phase, the wearable will be maintained in a monitoring mode and simply acquire data, providing no assistance/feedback on location and orientation. During the active phase, the wearable will have an activated assistive mode, i.e., the wearable will acquire data and simultaneously provide assistance/audio feedback. We will evaluate the effectiveness of the wearable for increasing navigation and quality of life. We hypothesize that the VIS^4^ION wearable will improve navigation and quality of life in individuals with visual disabilities.

During the active phase, subjects will complete their daily activities while wearing VIS^4^ION and using the mapping and localization microservice to facilitate wayfinding. Throughout the study we will monitor navigation performance through the same metrics as delineated in Aim 2 [week 2 compared to week 4], as well as to monitor for any falls that may occur (IMU-based alerting); we will also subjectively assess visual function through the 25-Item National Eye Institute Visual Function Questionnaire (VFQ25) [29], physical function and mobility, through the International Physical Activity Questionnaire (IPAQ) [30, 31], and QoL, through the World Health Organization QoL Brief (WHO-QoL-BREF) [32, 33]. The subjective assessments will be performed on day 0 (day of device delivery and initiation) and on the final day of the trial (day 31).

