### Adverse event reporting and harms {22}

Overall, the risk to participants is minimal: the likelihood of physical/psychological harm does not exceed what would be encountered in ordinary life. Subjects will be learning how to use a new assistive device and during this learning period, the subjects may be at a slightly greater risk of injury. Once the subject is accustomed to the device, the risk of injury would not exceed that in ordinary life.

The proposed psychophysical procedures pose no risk (the most likely negative consequence being boredom or fatigue). Subjects will be encouraged to rest should they feel any fatigue.

This risk is minimized through careful handling and storage of data and training of staff members. Subjects will be told to contact the PI if they experience a research-related injury. Should new information become available during the research that may affect a participant’s willingness to participate, all participants will be notified. Additionally, should any adverse effects of the procedures be demonstrated in the future, every attempt to notify participants will be made.

All adverse events will be immediately reported to the Ethics Committee.

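### The Aim 4 navigation window is weeks 1 and 4 in one section and weeks 2 and 4 in another, and only weeks 2 and 4 give the two sequences similar practice in active mode

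*Protocol article*

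**What the plan says.** Three places in the protocol article give a time window for the extended-use cohort.

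- Explanation for choice of comparators {6b}: comprehensive metrics will be used to "evaluate the outcomes in the first week and fourth week of extended use of wearables in passive and active phases".
- Abstract, Methods: "we will test another cohort of students for navigational, health, and well-being improvements, comparing weeks 1 to 4".
- Intervention description {11a}, Aim 4: navigation is followed with the Aim 2 metrics, "week 2 compared to week 4".

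Section {6b} does not name Aim 4, but extended use is Aim 4's own term: "A cohort of 20 (new) participants will be recruited to assess extended-use benefits over one month". Aim 4 is also the aim whose use period is set at one month, and so the one with a fourth week.

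The phase lengths are fixed in the same Aim 4 text: "During the first 15 days, group A will go through an active phase and then a passive phase for the next 15 days". Group B does the reverse, with 10 participants per sequence.

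The section on adverse events and harms {22} recognises a period of adjustment, "Subjects will be learning how to use a new assistive device", but gives no length for it. The questionnaires follow a different timetable in {11a}: day 0 and day 31.

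**The concern.** The article does not leave the navigation window to a later document. It fixes the window in two incompatible ways and does not say which prevails.

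The two windows are not interchangeable. Week 2 and week 4 both fall in the later part of their phase. Week 1 is the very start of phase 1, whereas week 4 is late in phase 2. Pairing week 1 with week 4 therefore scores active mode in new users in group A and in practised users in group B. Labelling each week by the mode worn does not repair this, because the imbalance lies in which days are scored.

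Two things are at stake. If benefit grows with practice, the active-mode estimate is diluted and the sequences differ in a way that resembles carryover. And while two windows stand in the text, either could be cited once data are in.

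**Working it through.** **Calendar mapping.** Phase 1 is days 1 to 15 and phase 2 is days 16 to 30 ({8} and {11a}). Days within phase 2 are study day minus 15.

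| Study week | Study days | Group A | Group B |
|---|---|---|---|
| 1 | 1–7 | active days 1–7 | passive |
| 2 | 8–14 | active days 8–14 | passive |
| 4 | 22–28 | passive | active days 7–13 (22−15 to 28−15) |

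At the start of week 4, group B has had six active days (16 to 21) after 15 days of wearing the device passively. On weeks 1 and 4 the scored active days are 1–7 (A) and 7–13 (B). On weeks 2 and 4 they are 8–14 and 7–13, a shift of one day.

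**Effect on the estimate.** Let τ be the trained active-minus-passive effect, taken as fully present in group B's week 4. Let f be the share of τ present in group A's first active week. f is an assumption; the documents give no value. Averaging the two sequences:

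½ × (fτ + τ) = τ(1+f)/2

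| f | Share of τ kept on weeks 1 and 4 |
|---|---|
| 1 | 100% |
| 0.9 | 95% |
| 0.75 | 87.5% |
| 0.5 | 75% |
| 0 | 50% |

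On weeks 2 and 4 the two sequences have nearly the same practice, so f is close to 1 and almost nothing is lost.

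**Difference between sequences.** Ignoring period effects common to both groups, the active-mode effect adds fτ to a group A participant's two-week total and τ to a group B participant's. The groups' totals then differ by (1−f)τ, in the comparison where carryover would also show.

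**A smooth alternative.** If benefit builds up as 1 − exp(−t/T), with T assumed between 1 and 30 days, the weeks 1 and 4 estimate is smaller than the weeks 2 and 4 estimate by 7% (T = 1), 18% (T = 3), 27% (T = 7) and 33% (T = 30).

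**Power, for illustration only.** The protocol states no power for Aim 4. Its one figure, at least 0.8 under Sample size, concerns the first phase: 20 subjects, a 40% difference in path length, and an SD of length ratios of 2.5. It reproduces if the SD is read as ln 2.5 on the log scale and the test is a one-sided 5% z-test:

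- |ln 0.6| / ln 2.5 × √20 = 0.511 / 0.916 × 4.472 = 2.49
- Φ(2.49 − 1.645) = 0.80 (a two-sided test gives 0.70)

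Multiplying 2.49 by (1+f)/2 gives power of about 0.77 at f = 0.9, 0.59 at f = 0.5 and 0.35 at f = 0.

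**The case against.** A reader might infer that half the effect will be lost. The documents do not support that. It needs f = 0, meaning no benefit at all in seven active days, and the protocol's own expectations point the other way. Aim 2 tests benefit on five active days straight after five passive days, and section {20a} anticipates better wayfinding in that active phase. The harms section mentions learning in connection with a slightly raised injury risk; it gives no duration and says nothing about navigation benefit. This part of the objection stands. It does not show that f equals 1, however. Aim 2 users reach active mode after five days of passive wear and group A does not, and an early benefit may still grow.

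The dilution formula and any power loss also belong to an averaged by-mode contrast that the protocol does not specify. For Aim 4, {20a} describes pre/post comparisons by Bayesian model comparison, and {8} calls the experiment exploratory. This stands too, so the power figures cannot be read as losses in the stated plan.

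The abstract's wording, "comparing weeks 1 to 4", can be read as start to end of the month. That leaves {6b} as the clear conflict with {11a}. Section {6b} is a rationale section, and the Aim 4 procedure already holds the balanced window, so loose wording is a plausible explanation. That bears on how the conflict arose; it does not remove it.

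Finally, an average that includes early use is a legitimate target. Unequal amounts of early use in the two sequences are still a fault under that target.

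**Conclusion.** The concern holds as an inconsistency in the navigation window for Aim 4, with a consequence that depends on which window is used. That weeks 1 and 4 give the sequences unequal active practice (days 1–7 against 7–13), and that weeks 2 and 4 nearly equalise it (days 8–14 against 7–13), follows from the protocol's own schedule without further assumption.

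The size of any bias does rest on assumptions: the unknown f, full benefit in group B by week 4, and an averaged active-minus-passive contrast. Under these, the effect kept on weeks 1 and 4 is 95% at f = 0.9 and 75% at f = 0.5. The 50% figure is the extreme bound, provided active mode does not worsen navigation in its first week; it is not an expected loss. If f is near 1 the dilution is small, and what remains is the need to settle the window before data exist.

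The point concerns the device-recorded navigation metrics. A reader might extend it to every Aim 4 outcome, but the questionnaires are set at day 0 and day 31, outside both windows, and the wearable does not record blood pressure or BMI.

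**What to change.** Before enrolment, which the Trial status section says has not started, state one window for the device-recorded navigation metrics: the second week of each phase, that is study weeks 2 and 4. Label each participant's week by the mode worn, since week 2 is the active week in group A and the passive week in group B. Align {6b} and the abstract with the Aim 4 text in {11a}. Report the first week of each phase separately, as a description of learning.

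The cost is wording in two places. No extra collection is needed for these metrics, because the wearable acquires data in both modes. The downside is that first-week data leave the main contrast. The timing of questionnaires, blood pressure and BMI is not settled by this change.
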